## Abstract

Supplemental Digital Content is available in the text

## Background

1

Intestinal neuronal dysplasia type B (IND-B) is a pathological entity of the group of gastrointestinal neuromuscular diseases characterized by complex alterations in the enteric nervous system.^[1]^ In 1971, Meier-Ruge^[2]^ described IND-B for the first time as a condition typically associated with distal intestinal obstruction that could mimic Hirschsprung disease (HD) but exhibited distinct histopathological characteristics. Since then, despite intensive scientific investigation, there remain inconsistencies with respect to the definition, etiopathogenesis, diagnostic criteria, and therapeutic possibilities of IND-B.^[3]^

IND-B is considered a rare disease, with an estimated incidence of 1:7500 live births.^[4]^ However, the frequency of IND-B varies widely, and the reported rates range from 0.3% to 40% of all rectal suction biopsies.^[5–8]^ The latest published series by Taguchi et al^[9]^ involved a retrospective multicenter study of IND-B cases in 167 centers in Japan between 2000 and 2009. These authors reported 13 cases based on standardized morphologic criteria from all of the included centers.^[9]^

The diagnosis of IND-B fundamentally depends on the histopathological analysis of rectum biopsies.^[10]^ However, the morphological criteria for its diagnosis have changed significantly over the years, rendering both diagnostic practice and study comparison difficult. Hyperplasia of the submucous nervous plexus is the morphological finding that defines IND-B, but specific morphological criteria may differ widely.^[2,11–14]^

Patients typically present with intestinal constipation, sometimes complicated by episodes of intestinal obstruction.^[3,15]^ In some cases, these symptoms may begin in the first days of life with a delay in meconium elimination, abdominal distension, vomiting, and feeding difficulties. Some patients continue to experience these symptoms throughout their lives, typically exhibiting severe intestinal constipation that is refractory to several types of treatments.^[16–18]^

The 2 therapeutic modalities include conservative clinical treatment and surgical treatment.^[19]^ Conservative treatment is based on changes in diet and the use of laxatives and enemas in cases of fecal impaction.^[3,20]^ Surgical treatment, on the other hand, may include sphincterotomy, colonic resection, or temporary colostomy.^[21–24]^ Nevertheless, the results of the different therapeutic modalities are conflicting, and follow-up studies are scarce and include only a limited number of patients. Most of these studies focus on only one modality of treatment and include short-term clinical follow-up. Therefore, only limited scientific evidence is available to establish a protocol to treat IND-B. However, in medical practice, we continue to identify children with severe intestinal constipation or bowel obstruction who undergo diagnostic investigation for HD with biopsies of the rectum that reveal submucosa nervous system hyperplasia compatible with the diagnosis of IND-B that require specific treatment.^[19]^ Therefore, we decided to assess the long-term clinical evolution of IND-B patients and compare the results obtained following conservative clinical and surgical treatments.

## Methods/design

2

### Study design and setting

2.1

This is a single-center, ambispective, observational, longitudinal, and comparative follow-up study to compare the results of conservative clinical and surgical treatments in patients with IND-B.

This study will be conducted at the Botucatu Medical School, São Paulo State University (UNESP), São Paulo, Brazil. Previous data will be recovered from the medical records of the study patients, including signs and symptoms present at the time of IND-B diagnosis, particularly those related to bowel habits, and treatments undergone. Later, these patients will be invited to participate in a semistructured interview during which aspects related to the long-term functional results of the bowel habit and quality of life will be investigated after a minimum interval of 5 years posttreatment.

### Ethics approval and consent to participate

2.2

This study will be conducted in accordance with the principles of the Declaration of Helsinki, ISO14155, Data Protection Act, and the Guidelines for Good Clinical Practice. The Research Ethics Committee (REC) of the Botucatu Medical School, UNESP, São Paulo, Brazil, has approved this study, which was registered under number 11520712.6.0000.5411 (see REC, Supplemental Digital Content 1). The patients and/or their guardians were previously informed of the purpose of the research, and each signed an informed consent form (ICF) (see ICF, Supplemental Digital Content 2). Patients aged 11 to 18 years signed the respective specific consent form (SCF) (see SCF, Supplemental Digital Content 3). All data will be sent to the REC at the end of the study. The subjects may leave this study at any point in time without any limitations.

The Brazilian Registry of Clinical Trials (Rebec) identifier for this study is RBR-8r3b7y, obtained on September 28, 2016 (UTN Number: U1111-1185-4950), available at http://www.ensaiosclinicos.gov.br.

### Eligibility criteria

2.3

The inclusion and exclusion criteria are presented in Table 1.

**Table 1 T1:**
[figure not shown]
Eligibility criteria.

### Patient selection, inclusion in treatment groups and recruitment

2.4

Sixty-three patients (<15 years) who received a diagnosis of IND-B at the University Hospital of Botucatu Medical School—UNESP between 1998 and 2012 will be included. The diagnosis of IND-B must have been established based on histopathological analysis of rectal biopsies or surgical specimens according to the morphological criteria proposed by the Frankfurt Consensus, 1990, with no additional associated dysganglionoses. These patients will be divided into 2 groups according to the type of treatment that they previously received: 29 patients in the surgical treatment group and 34 patients in the conservative treatment group.

The patients will be recruited through letters and phone calls and will be invited to attend the Clinical Research Unit (UPECLIN) of Botucatu Medical School—UNESP to participate in a semistructured interview.

### Pretreatment details (retrospective analysis)

2.5

Previous data will be recovered from patient medical records, including the age at which the symptoms appeared, age at the time of diagnosis, gender, gestational age and weight at birth, clinical evolutions during the neonatal period and the presence of associated malformations. The signs and symptoms, particularly those related to bowel habits, present at the time of IND-B diagnosis (before beginning treatment) and the treatments undergone will also be recovered. The following clinical information will be retrieved: number of evacuations per week, number of episodes of fecal incontinence per week, presence of retentive posturing during defecation, straining to pass stool, pain with defecation, presence of fecaloma, presence of abdominal distension, presence of bloody stools, presence of abdominal pains, and the need for enemas.

### Posttreatment data (clinical interviews)

2.6

Patients will participate in semistructured interviews to determine the functional results of the intervention with respect to patient bowel habits and quality of life after a minimum 5 years since the initiation of treatment. These interviews will be conducted by 2 pediatric surgeon members of the research team and will last approximately 40 minutes. The following assessment instruments will be applied: a questionnaire addressing current clinical status (Fig. 1), the Templeton & Ditesheim Scoring System (TDSS)^[26]^ to evaluate fecal incontinence (see TDSS, Supplemental Digital Content 4), the modified Bristol Stool Form Scale for Children (mBSFS-C)^[27,28]^ to analyze the consistency of feces (see mBSFS-C, Supplemental Digital Content 5), and the Pediatric Quality of Life Inventory version 4.0 (PEDsQL 4.0)^[29,30]^ to assess global quality of life (see PEDsQL 4.0, Supplemental Digital Content 6).

**Figure 1 F1:**
[figure not shown]
Questionnaire addressing the current clinical status.

### Outcomes

2.7

#### Posttreatment clinical status

2.7.1

The primary evaluation of the long-term clinical evolution of IND-B patients will be based on posttreatment data obtained during the clinical interviews. The analysis will be performed according to a classification of clinical prognosis as proposed by Tran et al^[31]^ (Fig. 2). In addition, the functional bowel habits assessed by the TDSS^[26]^ and mBSFS-C^[27,28]^ and quality of life assessed by the PEDsQL 4.0^[29,30]^ will be evaluated.

**Figure 2 F2:**
[figure not shown]
Classification of final status after treatment. Adapted from Tran et al^[31]^.

#### Evaluation before and after treatment

2.7.2

Data analysis will be performed by focusing on 2 assessment time points: assessment at diagnosis before the initiation of treatment and assessment at the time of interview, after a minimum period of 5 years after the treatment. This analysis will be performed using the following clinical variables: number of evacuations per week, number of episodes of fecal incontinence per week, presence of retentive posturing during defecation, straining and pain to pass stool, presence of fecaloma, presence of abdominal distension, presence of bloody stools, presence of abdominal pains, and need for enemas. In addition, based on the clinical information obtained in these 2 assessments, we will apply the Bowel Function Score (BF-S)^[32–34]^ (see BF-S, Supplemental Digital Content 7) and a proposed Intestinal Symptom Index (Fig. 3), with a variance from 0 to 7, which will identify the most common clinical complaints and symptoms during the clinical course of IND-B.

**Figure 3 F3:**
[figure not shown]
Intestinal Symptom Index.

#### Comparison between treatment modalities

2.7.3

The results obtained by the 2 treatment modalities (conservative clinical and surgical) will be compared with respect to the variables analyzed at both time points (before and after treatment) and with respect to the functional status and quality-of-life assessed after a long follow-up period. To summarize the stages of the study, see the flow diagram in Fig. 4 and the Supplemental Digital Content 8 with Standard Protocol Items: Recommendations for Interventional Trials (SPIRIT).

**Figure 4 F4:**
[figure not shown]
Flowchart of patients in the study.

### Statistical analysis

2.8

A statistical and descriptive analysis will be performed to interpret the clinical and demographic characteristics of the patients at the 2 time points of assessment. Continuous numerical data will be expressed as the mean ± standard deviation and median (minimum/maximum). Proportions will be presented as percentages and their respective reliability intervals. The comparison between the 2 treatment groups will be made using different statistical tests according to the types of variables analyzed. Nominal variables will be analyzed using Fisher exact test, and the Mann–Whitney *U* test will be used to analyze ordinal variables. The comparison between proportions will be made using the Binomial test. Continuous numerical variables of nonparametric distribution will be assessed using the Mann–Whitney *U* test. The analysis of global quality of life, assessed by means of the PEDsQL 4.0 questionnaire,^[29,30]^ will be compared to data previously published for a healthy pediatric population using the *t* test for differences between means. The significance level will be established at 5%, and the analysis will be performed using SPSS 22.0 for Windows.

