## Discussion

3

Few studies have reported the experience of IND-B patients, and most studies have focused on only one modality of treatment and included only short-term clinical follow-ups.^[17,18,21,35,36]^ Conservative clinical treatment must obey the general principles used in the treatment of children with chronic constipation and is focused on fecal disimpaction and laxatives at appropriate doses.^[37]^ Although it does not have a definite role like that in HD, surgical treatment may also be performed in IND-B patients.^[35]^ However, the surgical techniques used and the resected intestine segments vary significantly.^[15,19]^

Because IND-B is considered a rare disease, the proposed sample of 63 patients is considered satisfactory. Furthermore, one strength of this project is the possibility of comparing the results of the 2 treatment modalities proposed for patients with IND-B. This study is in the recruitment phase, which started in March 2015 and is still ongoing.

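### The surgical and conservative groups are not randomised and the reason for treatment choice is not given, yet only unadjusted tests are named, so baseline differences cannot be separated from a treatment effect

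*Protocol article*

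**What the plan says.** Section 2.1 of the protocol article calls the study a "single-center, ambispective, observational, longitudinal, and comparative follow-up study to compare the results of conservative clinical and surgical treatments". Section 2.4 forms the groups from past care: "These patients will be divided into 2 groups according to the type of treatment that they previously received", giving "29 patients in the surgical treatment group and 34 patients in the conservative treatment group". No reason for the choice of treatment appears in the text shown.

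Section 2.5 recovers pretreatment data from medical records, including age at symptom onset and at diagnosis, gestational age, associated malformations and bowel symptoms at diagnosis. Section 2.7.2 applies the Bowel Function Score (BF-S) and the Intestinal Symptom Index at diagnosis and again at interview, at least 5 years after treatment. Section 2.7.3 says that the results of the two modalities "will be compared with respect to the variables analyzed at both time points (before and after treatment"), and also on functional status and quality of life at long follow-up.

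Section 2.8 fixes the method: "The comparison between the 2 treatment groups will be made using different statistical tests according to the types of variables analyzed". The tests are Fisher exact for nominal variables, Mann-Whitney U for ordinal and non-normal continuous variables, and the Binomial test for proportions, at a 5% significance level. No regression, stratification, matching or weighting is named.

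**The concern.** In a non-randomised comparison, the groups may differ before treatment in ways that also predict the outcome. Each named test compares the groups as they stand and cannot allow for where they started. A before-treatment comparison may reveal a difference, but the plan gives it no role in the comparison at interview.

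A non-significant baseline test would be weak reassurance. With 29 and 34 patients, power to detect a 0.5 SD gap is about 51%.

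What is at stake is the interpretation of the between-group p-values. The comparison is one of the study's aims, and the Discussion presents it as a strength without mentioning confounding. If the groups started apart, a small p-value could reflect the starting difference, the treatment, or both, and the planned analysis cannot tell which.

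**Working it through.** **Inputs from the protocol article.** Group sizes are 29 and 34 (section 2.4), and 29 + 34 = 63, which agrees with the stated total. The significance level is 5% (section 2.8); sidedness is not stated and two-sided is assumed. The article gives no effect size, SD or power. The sample is justified by rarity: "Because IND-B is considered a rare disease, the proposed sample of 63 patients is considered satisfactory". There is therefore no planned power to reproduce.

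**Inputs assumed.** A baseline gap between groups (0 to 0.8 SD) and a baseline-outcome correlation r (0.3 to 0.5). Neither is in the document. The true treatment effect is set to zero.

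**Standard error of a standardised difference.** sqrt(1/29 + 1/34) = 0.253 SD.

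**Spurious difference.** Gap × r:
- low end: 0.5 × 0.3 = 0.15 SD
- high end: 0.8 × 0.5 = 0.40 SD

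**Rejection of a true null.** P(|Z + bias/0.253| > 1.96):
- low end: 0.15/0.253 = 0.59, probability 0.091
- high end: 0.40/0.253 = 1.58, probability 0.353
- no gap: 0.05

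**Check with the planned tests.** The formula above is for a normal test. A simulation with 29 v 34, normal data, zero true effect and 4,000 runs per scenario gives these rejection rates at nominal 5%. For the Fisher test the outcome was split at a fixed cut.

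| Gap (SD) | r | Mann-Whitney | Fisher | Baseline-adjusted regression |
|---|---|---|---|---|
| 0 | 0.3 | 5.0% | 3.9% | 4.7% |
| 0.3 | 0.3 | 5.7% | 4.4% | 4.8% |
| 0.3 | 0.5 | 8.8% | 6.6% | 5.0% |
| 0.5 | 0.3 | 8.5% | 6.4% | 4.4% |
| 0.5 | 0.5 | 16.5% | 10.8% | 5.4% |
| 0.8 | 0.3 | 14.9% | 9.9% | 5.0% |
| 0.8 | 0.5 | 31.8% | 20.0% | 5.1% |

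The Mann-Whitney rates follow the formula closely. Fisher is inflated less. Adjustment for the measured baseline keeps the rate near 5% with bias near zero, but only because in this simulation the measured baseline is the sole confounder.

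**Change scores as an alternative.** Under the same model, the expected group difference in change is gap × r − gap. At a gap of 0.5 and r = 0.5 this is 0.25 − 0.50 = −0.25 SD. Comparing changes would move the bias to the other side, not remove it.

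**The case against.** **The article is condensed and an SAP may exist.** Covariate lists and model form are often left to the SAP. That is fair as to detail. But section 2.8 states how the comparison will be made and names tests that take no covariate. A baseline-adjusted main analysis would replace that statement, not fill a gap in it.

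**The groups may be comparable.** This stands as a limit on what can be claimed. A reader might infer that surgery went to the more severe cases. The document does not say so: the groups are only "divided into 2 groups according to the type of treatment that they previously received", and the eligibility table and flowchart are not visible. The existence, direction and size of any imbalance are unknown.

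**The authors may not read the result causally.** A reader might infer that confounding will be reported as a treatment effect. The text does not support that certainty. It labels the study observational, plans a before-treatment comparison between groups and commits to STROBE reporting.

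**The study does not rest on this comparison alone.** This is correct. Long-term clinical status is the primary evaluation in section 2.7.1, and describing it needs no adjustment.

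**Adjustment is not a free gain in precision.** One might expect it to remove r² of the residual variance, 9% to 25% for r of 0.3 to 0.5. With a baseline gap, part of that is lost because treatment and baseline are correlated. At 0.8 SD the inflation is 1 + (29 × 34/63²) × 0.8² = 1 + 0.248 × 0.64 = 1.16. The net variance factor is 0.91 × 1.16 = 1.05 at r = 0.3 (a small loss) and 0.75 × 1.16 = 0.87 at r = 0.5. The reason to adjust is bias, not precision.

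**Conclusion.** The concern holds in a limited form. Treatment was not randomised, the reason for its choice is not described, and the only between-group tests named are unadjusted although baseline severity measures are planned. As section 2.8 stands, the comparison cannot separate a treatment effect from a difference present before treatment.

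The size cannot be known from the document. The range of about 9% to 35% false rejection is an illustration that rests on an assumed gap of 0.5 to 0.8 SD, an assumed correlation of 0.3 to 0.5, a normal test and a zero true effect. A smaller gap brings it close to nominal, and no gap gives about 5%. The conclusion about the method does not depend on those figures: nothing in the stated analysis would respond to an imbalance if one were found.

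**What to change.** In sections 2.7.3 and 2.8, prespecify one small baseline-adjusted comparison as the main between-group analysis.

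- For BF-S, the Intestinal Symptom Index and evacuations per week, use ANCOVA or rank-ANCOVA of the interview value on its own baseline. This is possible only for measures taken at both times. The TDSS, the stool form scale and the PedsQL have no planned baseline.
- For the final-status classification, use an ordinal model with treatment, one baseline severity score (the Symptom Index or BF-S, chosen in advance) and age at diagnosis. Name a single penalised method beforehand in case categories are sparse, so that the choice does not depend on the data.
- Report the adjusted difference or odds ratio with its 95% confidence interval.
- Keep the Fisher, Mann-Whitney and Binomial results as unadjusted and descriptive.
- Word the conclusions as association.

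The cost is modest but not nil. The change needs no new data items, but it uses a few degrees of freedom and brings model assumptions at n = 63, which supports only a few covariates. It depends on complete baseline entries in records for patients diagnosed between 1998 and 2012, and errors in those entries would leave residual confounding. Unmeasured confounding would remain in any case.

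### Quality of life is tested against a healthy pediatric reference with no stated age limit or matching, although the plan's own dates allow participants aged from about 5 to past 31 at interview

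*Protocol article*

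**What the plan says.** Section 2.4 of the protocol article (Patient selection, inclusion in treatment groups and recruitment) defines the cohort as "Sixty-three patients (<15 years) who received a diagnosis of IND-B at the University Hospital", with diagnoses made "between 1998 and 2012 will be included". Section 2.6 (Posttreatment data) places the interview, at which PEDsQL 4.0 is given, "after a minimum 5 years since the initiation of treatment". The Discussion dates the fieldwork: "This study is in the recruitment phase, which started in March 2015 and is still ongoing". Section 2.8 (Statistical analysis) then states that global quality of life on PEDsQL 4.0 "will be compared to data previously published for a healthy pediatric population using the" t test for a difference between means, at the 5% level.

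The text gives no upper age at interview, no age range for the reference population, and no age-banding, matching or adjustment for this test. Age at diagnosis is listed in section 2.5 as an item to collect, but its distribution is not reported. The eligibility table is not shown.

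**The concern.** A test against an external norm tells us about the disease only if the study sample and the reference are alike in other things that move the score. Age is an obvious one. The cohort was pediatric at diagnosis, but the outcome is measured years later, and the reference stays pediatric. If scores in healthy people differ with age, a gap from the norm (or the lack of one) may partly reflect the age of the participants and not IND-B.

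This is the only comparison with healthy people that section 2.8 describes, and quality of life is a named long-term outcome. A misleading result here would bear directly on what the study says about how these patients fare.

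**Working it through.** The article states no figure for age at interview, so there is nothing to reproduce. The check derives the age range from the dates and then the adult share under stated assumptions.

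**Inputs from the article.** Age at diagnosis under 15 and diagnosis in 1998-2012 (section 2.4); at least 5 years from start of treatment (section 2.6); interviews from March 2015, no end date (Discussion). The registry identifier was "obtained on September 28, 2016" (section 2.2). The article cites that date and says recruitment is still ongoing, so September 2016 serves as a second time point.

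**Assumptions.** Treatment starts at diagnosis. Diagnosis dates are uniform over 1998-2012. All 63 attend. Age 18 is taken as the top of a pediatric reference, since the article does not give its range.

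**Age range.** Age at interview = age at diagnosis + (interview date − diagnosis date).

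- Oldest, by calendar year: 14 + (2015 − 1998) = 31. With exact dates, a patient just under 15 at the start of 1998 is 15 + (2015.2 − 1998.0) = 32.2 in March 2015, and 15 + (2016.75 − 1998.0) = 33.75 in September 2016.
- Youngest: diagnosed at birth, 0 + 5 = 5.
- Anyone diagnosed in 1998: at least 2015.2 − 1999.0 = 16.2.
- Anyone diagnosed at 13 or 14: at least 13 + 5 = 18.

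The third line also rules out reading the under-15 limit as age at interview: nobody diagnosed in 1998 could meet it in 2015.

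**Age at diagnosis needed to be 18 in March 2015.** For diagnosis date y up to 2010.2 this is 18 − (2015.2 − y) = y − 1997.2. For later diagnoses the 5-year rule makes it 18 − 5 = 13. At the start of 1998 it is 0.8 years, of 2002 4.8, of 2006 8.8 and of 2010 12.8.

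**Adult share (18 or over at interview), by simulation.**

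| Assumed age at diagnosis | March 2015 | September 2016 |
|---|---|---|
| uniform 0-1 | 0.1% (0 of 63) | 8% (5) |
| uniform 0-2 | 2% (2) | 12% (7) |
| uniform 0-5 | 12% (7) | 22% (14) |
| uniform 0-10 | 28% (18) | 38% (24) |
| uniform 0-15 | 46% (29) | 55% (35) |

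Patients not yet at 5 years on the date shown are counted at 5 years.

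Hand check of the uniform 0-15, March 2015 cell: over the first 12.2 years of diagnoses the threshold runs from 0.8 to 13.0, mean 6.9, giving a share of (15 − 6.9)/15 = 0.54. Over the last 2.8 years the share is (15 − 13)/15 = 0.133. The weighted share is (12.2 × 0.54 + 2.8 × 0.133)/15 = 0.464, which agrees.

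**Illustrative effect on the test.** Suppose a fraction f of the 63 are adults, and adults differ from the pediatric norm by d SD through age alone. The mean shifts by f·d SD. Against a fixed norm with a two-sided 5% test, the chance of a false rejection is 1 − Φ(1.96 − f·d·√63) + Φ(−1.96 − f·d·√63).

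| f | d | Shift (SD) | False rejection |
|---|---|---|---|
| 0.1 | 0.2 | 0.02 | 5.3% |
| 0.3 | 0.3 | 0.09 | 11% |
| 0.5 | 0.3 | 0.15 | 22% |

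The values of f and d here are assumptions; the article supports none of them in particular.

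**The case against.** The strongest reply is that the dates show what ages are possible, not how common they are. The Background says symptoms can begin in the first days of life. If diagnosis was mostly in infancy and interviews took place early, there would be almost no adults and little bias: the first row of each table shows how small the problem could be. This stands. A reader might infer that many or most participants will be adults; the article does not support that, because it does not give age at diagnosis.

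Second, the size of any bias needs a difference in healthy scores by age, which the article does not supply. This also stands, so the comparison may be confounded; it is not shown to be, and it cannot be called uninterpretable.

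Third, a reader might infer that self-reports and guardian reports are mixed. Guardians appear in the article only in connection with consent, and nothing says who completes PEDsQL 4.0. That reading should not be pressed.

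Fourth, age-banding might be set out in the full protocol or an analysis plan, and the article does not say that the test is a single unstratified one on the whole cohort. This stands only in part. The article does fix the comparator population and the test, and that comparator does not match the ages its own dates allow. Age bands within a pediatric reference would still not cover a participant aged 31.

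Finally, the primary evaluation is the classification of clinical prognosis, with quality of life assessed in addition. That limits the consequence but does not remove it.

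**Conclusion.** The point holds in a limited form. The stated comparator does not fit the whole cohort: ages at interview can run from about 5 to 31 or more, and the test against healthy pediatric data carries no stated age restriction, matching or adjustment. Age is therefore an uncontrolled difference between the two samples, and the comparison may be confounded by it.

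The size is uncertain. Depending on age at diagnosis and interview date, the adult share runs from about 0 to about 35 of 63, if all attend and diagnoses were spread evenly over the period. The effect on the false-rejection rate could be negligible or a several-fold increase, depending on an age effect that has to be assumed. The change is worth making before analysis. The comparison of quality of life between the surgical and conservative groups does not use the norm and is not touched by this point.

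**What to change.** In section 2.8, state the age range of the published reference sample and limit the t test against it to participants whose age at interview lies in that range. Within the range, use age-banded norms, or a reference mean standardised to the study's own age mix, and give the difference with a 95% CI. Report participants above the range separately and descriptively, with no test against pediatric norms. Report the distribution of age at interview, so that a reader can see how many fall on each side.

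This changes analysis wording only; age at interview is already known and no new data are needed. The cost is fewer patients, and so a wider interval, in the comparison with norms.

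Suggested wording: *PEDsQL 4.0 scores will be compared with the published healthy reference only for participants whose age at interview is within the age range of that reference, with the reference mean standardised to the age distribution of these participants. The mean difference will be given with its 95% confidence interval. Scores of older participants will be summarised separately without a test against the reference.*

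### The surgical v conservative comparison spans about 16 unranked post-treatment outcomes at a 5% level, and the priority given to the prognosis classification is not carried over to it

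*Protocol article*

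**What the plan says.** Three places in the protocol article bear on this.

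- **Section 2.7.1, posttreatment clinical status.** "The primary evaluation of the long-term clinical evolution of IND-B patients will be based on posttreatment data obtained during the clinical interviews". The next sentence makes a prognosis classification (Fig. 2) the basis of that analysis. The TDSS, the stool form scale (mBSFS-C) and the PEDsQL 4.0 are introduced after it as additional. Treatment groups are not mentioned.
- **Section 2.7.3, comparison between treatment modalities.** The results of the two modalities "will be compared with respect to the variables analyzed at both time points (before and after treatment"), and also "with respect to the functional status and quality-of-life assessed after a long follow-up period". There is no order of priority.
- **Section 2.8, statistical analysis.** Tests are assigned by type of variable, and the section closes: "The significance level will be established at 5%, and the analysis will be performed using SPSS 22.0 for Windows". No outcome is singled out and nothing is said about several outcomes being tested.

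The variables measured at both times are listed in section 2.7.2: "number of evacuations per week, number of episodes of fecal incontinence per week, presence of retentive posturing during defecation, straining and pain" on passing stool, then "presence of fecaloma, presence of abdominal distension, presence of bloody stools, presence of abdominal pains, and need for enemas". The Bowel Function Score and the Intestinal Symptom Index are added there.

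**The concern.** Comparing the two modalities is the study's stated aim, and the discussion presents it as a strength. Yet the text does not say which result answers the question. An analyst following 2.7.3 and 2.8 to the letter would produce a column of about 16 post-treatment p-values, each read against 0.05, with nothing to say which one counts.

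With 29 surgical and 34 conservative patients, and scales that overlap, a report could favour surgery or conservative care on whichever outcome crossed the line. A reader could not tell a finding that was specified in advance from one picked afterwards. This matters in a rare disease with little comparative evidence, where such a result may be given much weight.

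**Working it through.** The article gives no power calculation or familywise error rate, so there is no derived figure to reproduce. The check is a count followed by an error calculation.

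**Step 1. Count the post-treatment between-group outcomes.**

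| Source | Outcomes | Number |
|---|---|---|
| 2.7.2, clinical variables | weekly stools, weekly incontinence episodes, retentive posture, straining, painful defecation, fecaloma, distension, blood in stool, abdominal pain, enema use | 10 |
| 2.7.2, scores | Bowel Function Score, Intestinal Symptom Index | 2 |
| 2.7.1 | prognosis classification, TDSS, mBSFS-C, PEDsQL | 4 |
| **Total** | | **16** |

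Section 2.7.2 runs straining and pain together, but section 2.5 lists them apart ("straining to pass stool, pain with defecation"). As one item they give 15. The count takes functional status in 2.7.3 to mean the prognosis classification, TDSS and stool form.

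**Step 2. Upper figure: independent tests, each with true size 5%, no true differences.** The chance of at least one p<0.05 is 1 − 0.95^m.

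- m = 16: 1 − 0.95^16 = 56.0%
- m = 15: 1 − 0.95^15 = 53.7%

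These count a false positive in either direction. For one named modality the figure is 1 − 0.975^16 = 33.3%.

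**Step 3. Fisher's test runs below 5%.** Its exact size at 29 v 34, by the true prevalence of the symptom in both groups:

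| Prevalence | 5% | 10% | 20% | 30% | 50% |
|---|---|---|---|---|---|
| True size | 1.2% | 2.6% | 3.1% | 3.5% | 4.3% |

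**Step 4. Allow for correlation and for Fisher's conservatism together.** All 16 outcomes were simulated at 29 v 34 with no group difference (3,000 runs per setting). Eight symptoms were tested by Fisher's test. The two counts, the scores and scales, and the prognosis classification were tested by Mann–Whitney. The symptom index was the sum of seven of the symptoms. The Bowel Function Score was not built from them, but shared the common correlation. The article gives neither correlations nor prevalences, so both are assumptions. The ranges below come from two sets of symptom prevalences, 10% to 30% and 30% to 50%.

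| Assumed correlation | Chance of at least one p<0.05 |
|---|---|
| 0 | 47% to 52% |
| 0.2 | 43% to 47% |
| 0.3 | 42% to 46% |
| 0.5 | 35% to 37% |
| 0.7 | about 30% |

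For correlations of 0.2 to 0.7 the range is thus about 30% to 47%. Against 5%, that is 30/5 = 6 to 47/5 ≈ 9 times the nominal rate.

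**Step 5. After the change.** With one designated comparison, the chance of a false positive on the deciding result is 5%. If all 16 were kept confirmatory instead, Bonferroni would test each at 0.05/16 = 0.0031. The familywise error would be 1 − (1 − 0.003125)^16 = 4.9% under independence, and at most 5% under any dependence.

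**The case against.** The strongest reply is that section 2.7.1 does name a primary evaluation, tied to one instrument, with the other scales set apart as additional. This stands in part. A reader might infer that the plan has no primary outcome at all, and the text does not support that. The gap is narrower: 2.7.1 speaks of the evolution of the patients as a whole, and 2.7.3 and 2.8 do not apply its ranking to the treatment comparison.

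A second reply is that a condensed article may leave multiplicity procedures to an analysis plan that is not shown, and that this is an observational study with no formal decision rule. The absence of a Holm or Bonferroni step is indeed no fault by itself. But the article does describe the treatment comparison, and describes it as an unranked list at one 5% level. Which outcome decides that comparison belongs in the protocol.

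A third reply concerns the size of the problem. A reader might infer that a chance finding is more likely than not. That needs nearly independent tests of close to 5% size. The outcomes are overlapping bowel symptoms, two of the scores are derived from the same clinical information, and Fisher's test falls short of 5% here. In the simulation the chance passed 50% only with uncorrelated symptoms at the higher prevalences.

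A reader might also count every test: 16 after treatment, 12 between groups at diagnosis, 12 before-after and 1 PEDsQL comparison with healthy norms, 41 in all. The last 25 cannot by themselves produce a false post-treatment advantage for one modality. Nor is it plausible that all of their null hypotheses are true, since the groups were formed by the treatment received and the before-after tests span at least 5 years. Only the 16 carry the argument.

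**Conclusion.** The point holds in this limited form. As written, the treatment comparison covers about 16 post-treatment outcomes without rank, and the priority given to the prognosis classification stops short of it. If no outcome truly differs, the chance of at least one nominally significant result in either direction is at most about 56% under independence. It is roughly 30% to 47% under the assumed correlations of 0.2 to 0.7 and the assumed symptom prevalences. The exact figure cannot be known from the article, but across these assumptions it is several times 5%. The weakness lies in how the comparison will be interpreted. It does not invalidate the design, and it can be put right before analysis.

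**What to change.** State in sections 2.7.3 and 2.8 that:

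1. the single primary between-group comparison is the final-status (prognosis) classification at interview, surgical v conservative, tested two-sided at 5%. Section 2.8 already provides a test for a nominal and for an ordinal outcome, so no new method is needed; say which applies.
2. all other between-group outcomes are secondary or exploratory, reported as estimates with 95% confidence intervals, and not used alone to claim that one modality is better.
3. any of these that is meant to support such a claim will be adjusted for multiplicity, for example by Holm's method. Which ones, if any, is for the investigators to choose and can be set out in the analysis plan.

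The cost is wording, handled under the amendment procedure in section 2.9. No further patients or data are needed. The downside is that results on single symptoms and secondary scales lose their stand-alone significance claim.
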